## Abstract

**Background:**

Severe mental illness (SMI) presents a major challenge worldwide, affecting approximately 5–8% of the world’s population. It causes significant distress to affected people, families and wider communities, generating high costs through loss of productivity and ongoing healthcare use. Over 75% of patients with psychosis receive inadequate care and experience a negative financial impact and reduced quality of life (QoL). It is therefore a priority to reduce the treatment gap by providing low-cost, effective interventions for people with psychosis.

Our research project, PIECEs, is designed to explore, adapt and test a low-cost, approach (DIALOG+) that makes use of existing resources to improve community-based care for patients with psychosis. The research will be conducted in two urban sites: Karachi, Pakistan and Chennai, India. DIALOG+ is a novel, technology-assisted and resource-oriented intervention, based on QoL research, concepts of patient-centred communication, IT developments and solution-focused therapy. However, the approach has not been rigorously tested within India and Pakistan. Our randomised controlled trial (RCT) aims to test the effectiveness and cost-effectiveness of DIALOG+ in improving the QoL and clinical outcomes for individuals with long-term psychosis being treated in the community in India and Pakistan.

**Methods:**

To assess the acceptability, feasibility, and cost effectiveness of DIALOG+, we will conduct a cluster RCT with 210 patients and 14 clinicians in each country. The intervention will be used during a routine interaction between a clinician and a patient. It consists of a patient-centred assessment (the DIALOG scale) whereby the clinician invites the patient to rate their satisfaction with different life domains and treatment aspects, which forms the active control group. The intervention group will follow this up with a four-step solution-focused approach to identify the patient’s resources and develop solutions to deal with the patient's concerns (DIALOG+).

**Discussion:**

If shown to be effective DIALOG+ has the potential to improve community-based care and the QoL for millions of people within India and Pakistan who experience psychosis.

**Trial registration:**

The trial was registered prospectively on the ISRCTN Registry: ISRCTN13022816 on 9 February 2022.

## Administrative information

Note: The numbers in curly brackets in this protocol refer to SPIRIT checklist item numbers. The order of the items has been modified to group similar items (see http://www.equator-network.org/reporting-guidelines/spirit-2013-statement-defining-standard-protocol-items-for-clinical-trials/).

## Introduction

### Background and rationale {6a}

Severe mental illness (SMI) presents a major challenge worldwide, affecting approximately 5–8% of the world’s population [1, 2]. SMI causes significant distress to affected people, families and wider communities, generating high costs through, for example, loss of productivity and ongoing health and social care use [3]. Within low- and middle-income countries (LMICs), there are neither sufficient financial resources nor qualified staff to provide extensive specialised services to people with SMI. As a result, an estimated 69–89% of people with SMI within LMICs experience a treatment gap [4, 5]. This treatment gap is most pronounced for psychosis, particularly long-term psychosis, where 75% of all individuals do not receive adequate care, despite the high financial impact and reduced quality of life (QoL) [3, 4]. It is therefore an urgent priority to reduce this treatment gap by providing low-cost, effective interventions for people with long-term psychosis [6].

The prevalence of mental health conditions in Pakistan is reportedly up to 34% [7]. Inadequate attention to mental health in the public sector has resulted in an estimated ratio of 2–3 psychiatrists per million people [8, 9]. A lack of mental health services and widespread poverty mean mental health issues often remain undiagnosed, misdiagnosed or untreated. In India, the estimated lifetime prevalence of mental disorders is 13.9% [10], with inadequate infrastructure, financial and human resources resulting in a ratio of 3 psychiatrists per million people. Care is reported to be inadequate for 70–75% for patients with psychosis in India [11].

Resource scarcity within healthcare systems in LMICs has led to calls for more stringent priority setting and allocation of available resources to ensure the most effective use. In high-income countries (HICs), evidence on the cost-effectiveness of innovative approaches to manage mental health conditions is routinely generated to inform policy makers. Studies in HICs confirm that community management of psychosis represents the best value for money and can result in future resource savings for the healthcare system [12–14].

A large proportion of people with psychosis in India and Pakistan live with their families as there are limited alternatives and welfare support [15]. Any care for people with psychosis is predominantly managed by limited conventional inpatient facilities, where patients can stay for long periods removed from their social context and without effective psychosocial interventions. A lack of qualified staff can limit the ability to provide services used in HICs such as multi-disciplinary teams or specialised psychological treatments (e.g. cognitive behaviour therapy). There is therefore a need for effective, appropriate and low-cost forms of care that utilise and strengthen existing personal and social resources available to individuals, families and communities.

This RCT sits in a wider programme of research, the PIECEs project, which aims to improve community services for people with long-term psychosis by adapting, testing and implementing a low-cost, approach called DIALOG+. The programme and RCT is being conducted in two urban cities: Karachi, Pakistan and Chennai, India. Approaches to community care shown to be effective here will have a high chance of success in other sites across the Indian subcontinent and, if successful, there is potential to improve community-based care and the QoL for millions of people within India and Pakistan who experience psychosis.

Previous research developed DIALOG+ which is an evidence-based approach to improve the quality of care for people with long-term psychosis, by utilising the existing resources available to patients within their families, community and healthcare services. DIALOG+ is a novel technology-assisted and resource-oriented intervention that is based on QoL research, concepts of patient-centred communication, IT developments and solution-focused therapy [16, 17]. The approach makes use of existing meetings between patients and clinicians, making them more effective. However, the approach has not been rigorously tested within India and Pakistan. This RCT aims to test the effectiveness and cost-effectiveness of DIALOG+ in improving the QoL and clinical outcomes for individuals with long-term psychosis being treated in the community in India and Pakistan.

### Objectives {7}

The cluster RCT has three main aims:To test the effectiveness of DIALOG+ as compared to an active control in improving the quality of life, clinical and social outcomes for individuals with long-term psychosis receiving community-based care in India and PakistanTo assess the cost-effectiveness of DIALOG+ from the healthcare perspectiveTo understand the experience and acceptability of DIALOG+ within routine services in India and Pakistan

### Trial design {8}

To test DIALOG+ within routine healthcare settings in India and Pakistan we are conducting a cluster RCT. The design of the cluster RCT was finalised after incorporating the results of a pilot study which informed local adaptation of the intervention.

The unit of analysis for the cluster RCT will be the mental health professionals, who will be recruited from outpatient clinics at three included clinical sites (two in Pakistan and one in India). The caseloads of the mental health professionals will be screened by researchers to identify potentially eligible patients. The clinician along with their enrolled patients will form individual clusters and will be allocated on a 1:1 basis to either the control (DIALOG scale) or the intervention arm (DIALOG+).

Assessors will be blinded to participant allocation for all data collection.

## Methods: participants, interventions and outcomes

### Study setting {9}

The research will be conducted in two urban settings: one outpatient clinic in Chennai, India (Schizophrenia Research Foundation - SCARF), and two facility centres in Karachi, Pakistan—a public-sector tertiary hospital (Jinnah Postgraduate Medical Centre—JPMC) and an outpatient clinic at a private mental health hospital (Karwan-e-Hayat- KeH).

### Eligibility criteria {10}

Inclusion criteria:

Individuals with psychosisAged 18–65 years oldDiagnosis of psychosis defined as an ICD-10 diagnosis of Schizophrenia, schizotypal, delusional and other non-mood psychotic disorders (F20-29) and/or bipolar disorder with psychotic features (F31.2, F31.5, F31.64)Currently not receiving inpatient treatmentDuration of illness greater than 2 yearsScore < 5 on Manchester Short Assessment of Quality of Life (MANSA)Capacity to provide informed consent based on an adapted ‘University of California, San Diego Brief Assessment of Capacity to Consent (UBACC)’ Scale score of 12 or aboveAbility to speak and understand the local language; Urdu (Pakistan), Tamil (India) or English

CliniciansAged 18 years or overHas regular clinical contact with individuals with psychosisExperience of working with individuals with psychosisNo plans to leave the current post within the next 6 monthsAbility to speak and understand the local language; Urdu (Pakistan), Tamil (India) or English

Family members/carersPrimary caregiver of a person with psychosis enrolled in the DIALOG+ RCT (primary caregiver defined as the main person responsible for helping with activities of daily living, supporting, and advocating on behalf of the patient)Has been the primary caregiver of a person with psychosis for more than 6 monthsAged 18–75 years oldAbility to speak and understand Urdu (Pakistan), Tamil (India) or English

Exclusion criteria:

Individuals with psychosisDementia and/or significant cognitive impairment cognitive impairment and/or severe learning disabilityOrganic psychosis or drug-induced psychosis if given as the primary diagnosisUnable to provide informed consent on the UBACC scale (score < 12)

Clinicians, family members/carersDoes not have regular contact with individual(s) with chronic psychosisUnable to speak either English, Urdu or Tamil

#### Who will take informed consent? {26a}

Potentially eligible patients will be approached by their clinicians to introduce the study to them. Individuals who respond to the study information with interest will be contacted and invited to attend a face-to-face meeting with a researcher who will provide them with further information. Researchers will go through consent forms (in their preferred language) with interested individuals and take time to answer any questions or concerns that are raised. All participants are asked to provide informed consent by signing and dating an informed consent form prior to any data collection commencing. The University of California, San Diego Brief Assessment of Capacity to Consent (UBACC) instrument will be used to rate the ability of individuals to provide informed consent. This form was adapted to our consent form and a score of 12 or above qualifies the patient to take part in the RCT. Once the ability to provide informed consent has been ascertained, participants will be provided with two copies of the written consent form, which will be signed by the participant and a member of the research team in order to proceed with study participation. The participant will keep one copy of the informed consent form and the research team will keep the other, storing it in a locked filing cabinet. Where participants are not literate, an additional witness will also be required to sign the consent form.

All researchers have received training based on Good Clinical Practice by members of the UK-based research team, senior members of the local research team and/or through online courses. If there are any doubts regarding the individual’s capacity to consent to take part in research, this will be resolved before proceeding with study participation. If any doubts about their capacity emerge during the recruitment process, or capacity to consent appears to change during their participation in the study, their capacity to consent will be re-evaluated before continuing with study participation.

#### Additional consent provisions for collection and use of participant data and biological specimens {26b}

Additional consent provisions are not applicable as no biological samples will be collected.

### Interventions

#### Explanation for the choice of comparators {6b}

In order to control for the novelty of a tablet computer within the consultation, and to control for the repeated measurement of quality of life, an active comparator (DIALOG scale) will be used within the trial. The DIALOG scale comprises 11 items made up of eight life domains (mental health, physical health, job situation, accommodation, leisure activities, friendships, relationship with family/partner, personal safety) and three treatment aspects (medication, practical help, meetings with professionals). Each item is rated on a scale from 1 (‘totally dissatisfied’) to 7 (‘totally satisfied’) and followed by a question on whether the patient wants additional help with that domain. Unlike the DIALOG+ intervention, clinicians will be instructed to ask participants to complete the scale at the end of the session, without further discussion and use of the four-stepped solution focused approach.

#### Intervention description {11a}

The intervention being tested is an evidence-based app mediated intervention called DIALOG+. The intervention and its training methodology has been adapted during a pilot phase and is now being tested within a cluster RCT.

DIALOG+ is used during a routine interaction between a clinician and a patient. It aims to better utilise the resources of the healthcare system by making these meetings more effective and by mobilising other existing resources available to the patient. It consists of a patient-centred assessment (the DIALOG scale) whereby the clinician invites the patient to rate their satisfaction with different life domains and treatment aspects. This is followed by a four-step solution-focused approach to identify the patient’s resources and develop solutions to deal with the patient's concerns. The intervention is available as an app and makes use of a tablet computer (e.g. iPad or Android device) within routine clinical meetings. Clinicians will receive training from the researchers in how to use the intervention, including how to support patients who are unfamiliar with a tablet computer.

Each session begins with the patient using the tablet to rate their satisfaction with eight life domains (mental health, physical health, job situation, accommodation, leisure activities, friendships, relationship with family/partner, personal safety) and three treatment aspects (medication, practical help, meetings with professionals). The tablet allows patients to be more actively involved in the meeting, with the tablet easily passed between the clinician and patient. Each satisfaction item is rated on a scale from 1 (‘totally dissatisfied’) to 7 (‘totally satisfied’) and followed by a question on whether the patient wants additional help with that domain.

The ratings are then summarised on screen, allowing for comparisons with ratings from previous meetings. Clinicians are instructed to offer positive feedback on any improving or high-scoring domains. The ratings are followed by a four-step solution-focused approach to identify the patient’s existing resources that can be used to address the concerns raised. The four steps are as follows: Understanding (Why is the patient dissatisfied? What went nevertheless well?); Looking Forward (What is the best case scenario? What is the smallest step forward?); Exploring Options (What can the patient, the clinician or others do?); and finally Agreeing on Actions (e.g. homework and referrals).

The intervention (both the DIALOG scale and DIALOG+) have already been translated into 16 different languages and for this particular trial, the app has been translated and adapted to use Urdu and Tamil script in Pakistan and India respectively.

Both the DIALOG scale in the control group DIALOG+ in the intervention group will be used once a month for 6 months which forms the active intervention period. Patients and clinicians will be actively followed up during this timeframe to ensure the sessions take place. After this period, there will be a 6-month flexible period where patients and clinicians can decide to use the intervention as per their discretion. This period will allow us to assess sustainability without researcher involvement and routine implementation of the DIALOG+ intervention.

#### Criteria for discontinuing or modifying allocated interventions {11b}

Although the intervention to be tested, DIALOG+, does not pose any risk to participants as evidenced by previous research, participants may experience anxiety in trying new interventions. Individuals will continue to receive their routine care, including any medication and psychosocial interventions that may be available. Furthermore, the intervention (DIALOG+) can be stopped at any point.

#### Strategies to improve adherence to interventions {11c}

Research coordinators will be assigned to monitor routine DIALOG+ appointments for all participants for the first 6 months of the intervention period. Researchers will actively assign appointments for the intervention/control sessions with participants and conduct reminder calls before a patient’s appointment to ensure maximum attendance.

The research teams will record attendance for all meetings in a ‘Meeting Record Log’ and data from the DIALOG+ app will be extracted on a monthly basis to monitor the duration and other details of the meeting.

To monitor further intervention fidelity, a random selection of sessions will be audio-recorded, and the DIALOG+ fidelity scale applied to measure adherence to the intervention and manual. Participants (both clinicians and patients) will be asked at the point of informed consent for additional consent to record sessions. It will be made clear to participants that this is optional, and consent will be confirmed prior to any sessions being recorded.

#### Relevant concomitant care permitted or prohibited during the trial {11d}

Individuals within both the control and intervention arms will continue to receive their usual care during the trial period. This includes access to routine services such as psychosocial interventions (where provided) and pharmacological interventions. We will, however, exclude individuals who are currently taking part in other RCTs of psychosocial interventions being conducted at the sites to reduce the potential for contamination.

#### Provisions for post-trial care {30}

It is highly unlikely that there will be any kind of harm suffered as a result of trial participation. In the very unlikely event that a participant discloses information regarding immediate risk to the self or others, their participation in that session will be immediately terminated and one of the researchers will inform the relevant safeguarding authorities (e.g. clinic). All researchers will be trained in safe-guarding procedures and will be provided with on-going supervision in policies and procedures for, and in working with, individuals who disclose risks of harm. All research activities will be completed by trained and qualified researchers with experience of working with people with mental health difficulties.

### Outcomes {12}

Quantitative outcome measures will be collected at 3 different timepoints: baseline, 6 months post randomisation and 12 months post randomisation. The primary outcome will be quality of life assessed via the Manchester Short Assessment of Quality of Life (MANSA) [18] score at 6 months post randomisation. Mean scores 6-month post randomisation will be calculated controlling for baseline scores and then compared between the two groups to assess the impact of the intervention.

Secondary clinical outcome measures include the psychiatric symptom severity score via Brief Psychiatric Rating Scale (BPRS) [19], negative symptom severity score via the Scale for Assessment of Negative Symptoms (SANS) [20] and disability measure via World Health Organization Disability Assessment Schedule (WHODAS) by proxy [21].

Secondary social outcome measures include the objective social situation score via Social Situation Index (SIX) [22] and therapeutic alliance for patients and clinicians via the Helping Alliance Survey (HAS) [23] score. The Burden Assessment Schedule [24] (in Pakistan) and The Burden Assessment Scale [25] (in India) will be used to measure burden experienced by carers.

Further secondary measures to evaluate the cost effectiveness of the intervention include health-related Quality of Life score via European Quality of Life version 5 (EQ5D-5L) [26] and adapted version of the Client Service Receipt Inventory (CSRI) [27].

The baseline assessment will also include a socio-demographics questionnaire for all participants. Sociodemographics will be summarised as means and proportions.

For all measures, the mean scores at 6 months and 12 months post randomisation will be calculated and compared between the intervention and control group, with the baseline values of each outcome included as covariate.

A subset of 20 patients per country and all 7 clinicians who were randomised to the intervention arm will be invited to attend a qualitative interview after the end of the intervention (6 months) in order to capture the individual experience of the intervention, including barriers and facilitators of attending intervention sessions, suggested adaptations and the practical delivery of the intervention. These interviews will be conducted with the help of a semi-structured topic guide and will be audio recorded. Interviews will be conducted at the end of the intervention (6-month post randomisation) to ensure ease of recollection of the specifics of the intervention, without influencing data collection of the primary outcome.

To maintain blinding of researchers within the study, monitoring of intervention fidelity and the qualitative follow-up interviews will be conducted by researchers who are aware of allocation. The other researchers will conduct the follow-up quantitative assessment and will remain blinded to intervention allocation. Participants and mental health professionals will be asked not to disclose details of the intervention during the follow-up quantitative assessments.

#### Participant timeline {13}

A summary of the participant timeline including a schedule for enrollments, intervention sessions and assessments can be found in Fig 1.

**Fig. 1 Fig1:**
[figure not shown]
The schedule of enrolment, interventions, and assessments for participants in the DIALOG+ study at all sites in India and Pakistan

### Sample size {14}

#### Quantitative sample size

In order to detect a medium effect size of 0.5, setting power at 90% for 5% significance, accounting for clustering based on an ICC of 0.002 (as observed within the DIALOG+ trial [15]), and applying a conservative design effect of 1.03, the total number of patients required in each country is 84 per group (*n* = 168 per country). After allowing for a drop-out rate of 20%, a total of 210 patients will need to be recruited to give the analysable sample of 168 or 84 per group. Therefore, 14 clinicians will need to be recruited in each country, with an average of 15 patients per clinician.

Clinicians of any background, including lay community workers will be eligible. Meetings held within each of the participating clinical services indicated that there were sufficient numbers of both clinicians and patients, with many outpatient clinics seeing 100+ patients with psychosis per day.

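### The 84 per group said to include the 1.03 design effect is the number before it; with 1.03 applied the requirement is 87, and power at 84 is about 89%, not 90%

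*Protocol article*

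**What the plan says.** The section on quantitative sample size gives the calculation for each country in one sentence. The target is set by "In order to detect a medium effect size of 0.5, setting power at 90% for 5% significance". Clustering is brought in by "accounting for clustering based on an ICC of 0.002", taken from an earlier DIALOG+ trial. The result is then given as "applying a conservative design effect of 1.03, the total number of patients required in each country is 84 per group", or 168 per country. Allowing for 20% drop-out brings this to 210 recruited, and the section concludes that "14 clinicians will need to be recruited in each country, with an average of 15 patients per clinician".

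The section on quantitative data analysis plans a mixed-effects model for MANSA at 6 months, with clustering by clinician and baseline MANSA as a covariate. The sample size section takes no credit for the baseline covariate and gives no correlation between baseline and follow-up.

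**The concern.** A design effect multiplies the sample size that an individually randomised trial would need. For a difference of 0.5 SD at 90% power and two-sided 5%, that unclustered number is itself about 84 per group. If 84 is also the answer after multiplying by 1.03, one of the two statements must be wrong.

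This is the one step in the calculation that allows for randomising clinicians rather than patients. The target is set per country, so a non-significant result in India or in Pakistan would be read against the stated 90%. It is therefore worth knowing whether the allowance was made and, if not, how much power is lost.

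**Working it through.** **Inputs.** From the sample size section: difference 0.5 SD, power 90%, significance 5%, ICC 0.002, design effect 1.03, drop-out 20%, 14 clinicians per country, 15 patients per clinician. Allocation is 1:1 (Sequence generation). Sidedness is not stated; two-sided is assumed, and one-sided is checked below.

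**1. Reproduce the stated figure without clustering.**
n = 2(1.960 + 1.2816)² / 0.5² = 84.06 per group.
This is the protocol's 84, rounded down. The t-test gives 86.

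**2. Apply the stated design effect.**
84.06 × 1.03 = 86.6, so 87 per group.
2 × 87 = 174 analysable; 174 / 0.8 = 217.5, so 218 recruited per country.
By the t-test the requirement is 88 per group: 176 analysable and 176 / 0.8 = 220 recruited.

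**3. See whether another reading yields 84.**
- One-sided 5% with 1.03 gives 71 per group.
- Design effect from 15 per clinician: 1 + 14 × 0.002 = 1.028; 84.06 × 1.028 = 86.4, so 87.
- Design effect from 12 analysed per clinician (15 × 0.8): 1 + 11 × 0.002 = 1.022; 84.06 × 1.022 = 85.9, so 86.

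None of these gives 84.

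**4. Check the later steps.** 168 / 0.8 = 210 and 210 / 15 = 14. Both are right, so the slip lies only in the design-effect step.

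**5. Power of what is planned.** The effective number per group is 84 / 1.03 = 81.55. The expected test statistic is 0.5 × √(81.55 / 2) = 3.193.
- Normal formula: Φ(3.193 − 1.960) = 89.1%.
- t-test on 166 df: 88.8%.

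**6. Gain from baseline adjustment.** If 0.5 is in units of the unadjusted SD, adjustment for a baseline with correlation r multiplies the required number by (1 − r²). The break-even is 86.58 × (1 − r²) = 84, so r = √(1 − 84 / 86.58) = 0.17. At r = 0.18 the requirement is 83.8 per group and power is 90.1%. At r = 0.2 it is 83.1 and 90.3%. These correlations are assumptions, because the protocol gives none.

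**7. Sensitivity to the number of clusters.** With 14 clinicians per country, a cluster-level t reference would have 14 − 2 = 12 df. Unadjusted power on that reference is:

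| Per group | Design effect | Power on 12 df |
|---|---|---|
| 84 | none | 84.4% |
| 84 | 1.03 | 83.4% |
| 87 | 1.03 | 84.6% |

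On 12 df a baseline correlation of about 0.43 would be needed to reach 90% at 84 per group.

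**The case against.** The best defence is that the slip is very small. It amounts to three analysable patients per group and about one percentage point of power, and the primary model already adjusts for baseline MANSA, where even a modest correlation would more than make up the loss. That stands, and it is why this is a minor correction. It does not make the sentence right: the text says the design effect is in the 84, and it is not.

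Three stronger readings are tempting, and the document does not support them.

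- **That true power is about 83%.** This figure comes from a 12-df reference, not from the omitted design effect: step 7 shows 84.4% with no design effect at all. The protocol specifies a mixed-effects model, names no degrees-of-freedom method and leaves further detail to the analysis plan. The figure also ignores the baseline covariate. It is a sensitivity remark only.
- **That power is far lower because the ICC could be 0.01 to 0.05.** The only ICC in the document is 0.002. Larger values would be the reader's own assumption and would show no error in the stated calculation.
- **That calling 1.03 conservative is wrong.** It lies slightly above both 1.028 and 1.022. The margin is little more than rounding, but the word is not false.

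**Conclusion.** The stated 84 per group is the number for an individually randomised trial, and the claim that it includes a design effect of 1.03 is incorrect. With 1.03 applied, the requirement is 87 per group (174 analysable, about 218 recruited per country), against 84, 168 and 210 as written. Power per country at 84 per group is about 89% (89.1% normal, 88.8% t) rather than 90%, before any gain from baseline adjustment.

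This rests on a two-sided 5% test, the protocol's own ICC and design effect, and exactly 20% drop-out. It is a minor arithmetic error in a figure that the trial relies on. A reader might infer that the trial is materially underpowered; the document does not establish that, because the shortfall is about one point and the planned baseline covariate may well recover it.

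**What to change.** Do not enrol more patients; correct the statement. Say that 84 per group is the number before the design effect, and then do one of the following:

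- restate power per country as about 89% without baseline adjustment; or
- keep 90% and state the assumed correlation between baseline and 6-month MANSA that supports it through the planned adjustment (about 0.18 by the normal formula), making clear that 0.5 is in units of the unadjusted SD.

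Optionally add a caveat, not presented as the corrected power: with 14 clinicians per country, a cluster-level t reference on 12 df would give about 83% unadjusted power and would need a correlation of about 0.43 to reach 90%.

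The cost is a change of wording. Recruitment, conduct and analysis stay as they are, and the stated power becomes slightly less favourable unless a correlation is given.
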